## Methods

### Study design

This study is a parallel multi-center randomized controlled trial for comparing the efficacy of a three- versus five-session counseling intervention on bereaved people who had lost a loved one due to COVID-19 by dividing them into two equal intervention groups.

### Inclusion and exclusion criteria

The participants are first-degree relatives of those deceased due to COVID-19, ranging from 15 to 64 years old. According to the study protocol, following 1 week after the occurrence of the death of a COVID-19 patient, a phone call will be made to connect with a family member of the deceased to initially assess them regarding the inclusion criteria. If the individual is eligible and willing to participate, the grief counseling sessions will be started 2 weeks after the death of the loved one. Participants should be literate and be able to understand and speak the Persian language. They should all give written informed consent to enter the study. If an individual has received any type of mental health service, including biological or non-biological therapies or interventions throughout this 2-week period, or if the individual has a severe comorbid medical or neurological condition along with disability, or fulfills the criteria of any psychiatric disorder, they will be excluded from the study. Serious suicidal ideation, suicidal attempts and a history of self-harm, and being diagnosed with any substance use disorder are also among the exclusion criteria. If a participant enters the counseling process and any of these exclusion criteria come up in the middle of the study; in that case, that individual will be excluded from the study but the necessary and standard therapy will not be withheld.

### Setting

This study will be conducted in the setting of 20 health centers affiliated with 10 of the universities of medical sciences of Iran, which are responsible for health services and medical education in their catchment area (including Ahvaz, Arak, Golestan, Guilan, Iran, Kerman, Mashhad, Shiraz, Tabriz, and Tehran universities). In each university, two health centers will be selected. These centers routinely offer basic mental health services by master clinical psychologists. A specific number of clinical psychologists of these centers will be further trained in a 2-day online workshop. In this workshop, psychologists learned how to perform three- and five-session mourning counseling according to a protocol by an expert panel to provide the intervention in a uniform and coordinated manner.

### Intervention

The content of grief counseling was provided by an expert panel, including psychiatrists and psychologists with experience in this field. Its stages include a literature review about the method of mourning during the COVID-19 pandemic, psychosocial consequences of COVID-19, types of grief, interventions related to grief counseling and treatment of traumatic bereavement, preparation of an initial intervention package with an emphasis on the COVID-19 pandemic, editing the package after the implementation of the pilot intervention and based on the opinions of the interveners and the target group. A service package has been developed to help the bereaved people of those deceased due to COVID-19 to go through the normal grieving process. This intervention package mainly focuses on the items below:

-To facilitate the acknowledgment and acceptance of the recent loss.-To help the participant cope with the pain and anguish of the recent loss.-To assess the participants’ defense mechanisms and approaches toward the recent loss.-To mutually explore finding some sort of meaning in the painful event.-To empower the participants to manage difficult situations and adjust to normal life.-To enable participants to be able to live in the absence of the lost one and to learn coping and problem-solving skills.-To find a way to be comfortable in life while keeping bonds with the lost one.

In both intervention methods, each session takes 45 min. Each session starts and ends with reviewing and presenting assignments. In both intervention groups, if the participant misses a session, the psychologist will call them two times at two different times on two different days to ask about the reason for their absence in the session. In case the participant is not willing to cooperate further, they will be excluded from the study.

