#### The five-session intervention group

In the five-session intervention, sessions will be held once a week, and the topics of the sessions will be as follows:

1.Session 1: Psychological assessment and preliminary consultation; creating a therapeutic alliance, and collecting demographic information.2.Session 2: Open evaluation of the event and acceptance of the loss; narrative of death (talking about the events related to death by the bereaved), mourning narrative (talking about the mourning ceremony), and evaluating the dominant emotions such as anger, disappointment, anxiety, sadness, and missing.3.Session 3: Learning to cope with the loss and searching for meaning in loss; explanation about the usual methods of dealing with grief: effective and inefficient methods, discussing the bereaved confrontation with the grief, and explanations about the meaning.4.Session 4: Recovery and adjustment to normal life in the absence of the deceased; the role of the deceased person in the life of the bereaved, the problems ahead after the loss, reviewing the usual method of solving problems, and teaching problem-solving techniques.5.Session 5: Assessment of the bereaving process and returning to life in the absence of the lost one; examining the feelings and emotions experienced, feelings about self, examining behavioral changes in self-care and relationships, and examining the change in attitude toward goal setting for the future.

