### Randomization

After informed consent, participants are randomized into three- or five-session intervention groups. Allocation of participants to each group will be done with the use of Stratified Balanced Block Randomization. Twelve participants will be selected from each university, and randomization will be done separately for each. Among 20 possibilities for six blocks including forms of three individuals in the five-session group and three individuals in the three-session group, two blocks will be randomly chosen for each university in the Microsoft Office Excel software with the use of the RANDBETWEEN formula and a random sequence will be formed. Subsequently, participants will be divided into the three- and five-session groups equally according to the random sequence. Randomization will be done in the main research headquarters in the Mental Health Research Center of the IUMS, and information will be only given to the health centers at the time of initiation of the intervention.

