#### Reducing loss to follow-up

For decreasing loss to follow-up of the participants, their phone numbers will be obtained at the beginning of the counseling sessions, and before each assessment, they will be reminded by phone 1 week before. If the participant does not attend, two follow-up telephone calls will be made. Calls will be at different times on different days, so the possibility of reaching the participant will increase. If, after two telephone calls, the participant is not willing to cooperate, the rater will try to fill out the GIS by phone and end the assessment.

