### Planned analysis

The data, after entering and cleaning, will be analyzed using the SPSS V.18 and Stata V.11 software. Mean and standard deviation will be calculated to continuous data and frequency, and percent will be used for showing categorical variables. The analysis approach will be “intention to treat.” An independent and paired *t*-test, a chi-square, and a repeated-measures ANOVA (non-parametric tests if necessary) will be used to compare the studied outcomes in the follow-ups between and within the groups. The generalized estimating equations (GEEs) will be fitted in separate models for each outcome, and α < 0.05 will be considered as statistical significance.

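### Two conduct rules exclude randomised participants from the study, which conflicts with the stated intention-to-treat analysis and, for one rule, drops people whose mental state has worsened

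*Protocol article*

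**What the plan says.** All references are to the protocol article.

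- **Randomization:** "After informed consent, participants are randomized into three- or five-session intervention groups". Anything that happens during counselling therefore happens to randomised people.
- **Intervention:** "In both intervention groups, if the participant misses a session, the psychologist will call them two times", and then "In case the participant is not willing to cooperate further, they will be excluded from the study".
- **Inclusion and exclusion criteria:** if an exclusion criterion comes up after counselling has begun, "that individual will be excluded from the study but the necessary and standard therapy will not be withheld". The criteria include any psychiatric disorder, severe medical or neurological comorbidity with disability, and "Serious suicidal ideation, suicidal attempts and a history of self-harm, and being diagnosed with any substance use disorder". Receipt of a mental health service is also listed, but only for the two weeks after the death.
- **Planned analysis:** "The analysis approach will be “intention to treat". The article does not define the analysis set further.
- **Reducing loss to follow-up:** for someone who misses an assessment and is unwilling after two calls, "the rater will try to fill out the GIS by phone and end the assessment".
- **Sample size calculation:** 60 per arm, effect size 0.5, drop-out 20% overall, not split by arm or reason.

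**The concern.** Intention to treat needs an outcome to be sought from everyone randomised, whatever counselling they received. Two conduct rules instead take randomised people out of the study, and neither says that they stay in follow-up or in the analysis. A statistical analysis plan cannot repair this, because it cannot recover outcomes that were never collected.

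The rule on emerging exclusion criteria matters more. Someone who develops a psychiatric disorder or serious suicidal ideation during counselling is close to being a treatment failure, in a trial whose Discussion gives prevention of psychological problems as the objective. Dropping such people improves the apparent result of whichever arm they were in.

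The stakes are higher because the hypothesis is that three sessions are comparable to five, and a finding of similar efficacy would support offering three sessions as a population-based service. Losing non-completers and deteriorating cases can hide a real difference or create a false one.

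**Working it through.** **1. The passages side by side.** Randomisation comes after consent and before counselling. Both exclusion rules operate during counselling, so both remove randomised people. Planned analysis says intention to treat. The telephone rule is triggered by a missed assessment; it does not say whether it reaches someone already excluded for a missed session or an emerging criterion. The conflict follows from the text alone and needs no arithmetic.

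**2. The plan's own figures.** The 60 per arm can be reproduced as a one-sided normal-approximation calculation: 2 × (1.645 + 0.842)² / 0.5² = 49.5, rounded up to 50, and 50 × 1.2 = 60. That basis is a separate matter and does not affect this point. The only figure on losses is 20% overall, or 12 of 60 per arm if equal.

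**3. Effect within each arm.** Assume that the excluded are the fraction *f* highest on a normal severity score that correlates ρ with the 3-month GIS. The mean GIS of those left falls by ρ × φ(z)/(1 − *f*) SD, where z is the (1 − *f*) normal quantile. At *f* = 0.20, z = 0.842, φ(z) = 0.280 and φ(z)/(1 − *f*) = 0.35. Each arm then looks better by 0.35ρ: 0.105 SD at ρ = 0.3, 0.175 at 0.5 and 0.245 at 0.7. With equal removal the difference between arms is unbiased.

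**4. Could removal be unequal?** After the first session, four sessions remain in one arm and two in the other. With an assumed constant risk *p* at each, the share excluded is 1 − (1 − *p*)⁴ versus 1 − (1 − *p*)²:

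| *p* (assumed) | Five sessions | Three sessions |
|---|---|---|
| 2% | 7.8% | 4.0% |
| 5% | 18.5% | 9.8% |
| 8% | 28.4% | 15.4% |

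If risk follows calendar time instead, weekly sessions × 5 and fortnightly sessions × 3 both span about 4 weeks (4 × 1 and 2 × 2), and the expected shares are equal.

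**5. Between-arm bias if removal is unequal and related to severity.** This uses the formula in step 3, with splits that average the planned 20%. At 25% versus 15%, φ(z)/(1 − *f*) is 0.424 and 0.274, a difference of 0.149. The session model in step 4 averages 20% at about 26% versus 14%, where the difference is 0.180.

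| Split (five vs three) | ρ = 0 | ρ = 0.3 | ρ = 0.5 | ρ = 0.7 |
|---|---|---|---|---|
| 20% vs 20% | 0 | 0 | 0 | 0 |
| 25% vs 15% | 0 | 0.045 | 0.075 | 0.105 |
| 26% vs 14% | 0 | 0.054 | 0.090 | 0.126 |

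These values favour five sessions. Taking strictly the most severe is the sharpest form of selection. A more extreme 30% versus 10% split would give 0.09 to 0.21 SD over the same non-zero ρ, but four sessions against two cannot produce a threefold ratio.

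**6. A softer selection model.** Let the odds of exclusion at each later session double per SD of grief, with the average risk set to 3%, 5% or 8%. The bias is 0.04, 0.06 and 0.09 SD in favour of five sessions if that grief score is the 3-month GIS itself, and about 0.02 to 0.04 SD if the two correlate 0.5. If the odds halve per SD, so that those doing better leave, the 5% case gives 0.06 SD the other way.

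**The case against.** The missed-session rule is not exclusion for absence alone. It applies after two calls and a stated unwillingness to go on, which is close to the voluntary withdrawal that the article allows and that the 20% drop-out allowance anticipates. This stands in part: the rule on emerging criteria is the stronger ground. But declining further sessions is not the same as refusing follow-up, and the text does not separate them.

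The telephone rule may already cover these people, since it uses similar language about unwilling participants. A reader might infer that no GIS is taken after exclusion and that intention to treat is impossible. The article does not say so; it leaves the matter unclear. The ambiguity still needs resolving.

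A reader might also infer that removal is unequal and flatters five sessions. The documents do not establish this. One rule covers both arms, both schedules last about 4 weeks, no rate by arm is given, and the sign reverses if those who stop are doing better. If three sessions worked less well, the emerging-criterion rule could remove more people from that arm.

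Nor is every trigger a bad outcome of grief. Severe medical or neurological comorbidity is not, and the mental-health-service criterion is limited to the two weeks after the death. The point rests on psychiatric disorder, suicidality and substance use disorder.

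**Conclusion.** The contradiction is real and rests on the text alone: randomised participants are excluded from the study under two rules while the analysis is called intention to treat, and nothing says that their outcomes will still be sought. Because several triggers are close to the outcome, following the rules as written can make both packages look better and can distort or mask a difference between them.

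The size is less certain. Unequal removal is plausible from the session counts but remains an inference. Under assumed unequal, severity-related removal the between-arm bias is roughly 0 to 0.1 SD, up to about a fifth of the planning effect of 0.5 SD (0.1/0.5), in a direction that depends on who leaves. It is zero if removal is equal by arm in rate and kind, or unrelated to outcome. It should be settled before follow-up, since uncollected outcomes cannot be recovered at analysis.

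**What to change.** Reconcile Inclusion and exclusion criteria, Intervention, Reducing loss to follow-up and Planned analysis, so that exclusion or stopping under the first two does not end outcome follow-up:

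- Seek the GIS at 1 and 3 months from these participants, by the existing telephone route if needed, unless consent to follow-up is withdrawn.
- State that the telephone route covers them.
- Analyse everyone randomised in the allocated arm.
- Record the reason and date of stopping, and report them by arm, so that any imbalance can be seen.

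The clinical handling of these participants stays as the protocol states it. The cost is an amendment to the wording of these sections and a few more telephone interviews by raters already in place.

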#### The five-session intervention group

In the five-session intervention, sessions will be held once a week, and the topics of the sessions will be as follows:

1.Session 1: Psychological assessment and preliminary consultation; creating a therapeutic alliance, and collecting demographic information.2.Session 2: Open evaluation of the event and acceptance of the loss; narrative of death (talking about the events related to death by the bereaved), mourning narrative (talking about the mourning ceremony), and evaluating the dominant emotions such as anger, disappointment, anxiety, sadness, and missing.3.Session 3: Learning to cope with the loss and searching for meaning in loss; explanation about the usual methods of dealing with grief: effective and inefficient methods, discussing the bereaved confrontation with the grief, and explanations about the meaning.4.Session 4: Recovery and adjustment to normal life in the absence of the deceased; the role of the deceased person in the life of the bereaved, the problems ahead after the loss, reviewing the usual method of solving problems, and teaching problem-solving techniques.5.Session 5: Assessment of the bereaving process and returning to life in the absence of the lost one; examining the feelings and emotions experienced, feelings about self, examining behavioral changes in self-care and relationships, and examining the change in attitude toward goal setting for the future.

#### The three-session intervention group

In the three-session intervention, sessions will be held every 2 weeks, and the topics of the sessions will also be as follows:

1.Session 1: Psychological assessment and preliminary consultation; creating a therapeutic alliance and collecting demographic information.2.Session 2: Open evaluation of the event and acceptance of the loss, expanding understanding of the recent loss, learning to cope with the loss and searching for meaning in loss; flexible assessment of the event and increased understanding of the reality of loss/coping with grief, increasing understanding of the reality of loss and coping with the pain caused by loss, examining defenses and countermeasures, and helping survivors find meaning in painful experiences.3.Session 3: Recovery and adjustment to normal life in the absence of the lost one; recovery, adaptation, and return to life without the deceased, helping survivors adjust to loss through problem-solving, returning to life, and examining the changes according to their narrative.

### Recruitment process

Five of the researchers will be in direct connection with the 10 medical universities. In every university, two health centers will be selected for service delivery, and one trained clinical psychologist will be the service provider in each center. The clinical psychologist obtains names and phone numbers of bereaved people on a routine basis from the social service department of the hospitals in the catchment area of the center and will invite them by phone to encourage them to attend the grief counseling sessions. The clinical psychologist will also try to create effective communication and express compassion and empathy toward the grieving individuals. When participants attend health centers, their demographic data are obtained and registered, and the inclusion or exclusion criteria will then be re-assessed. If inclusion criteria exist and in the absence of the exclusion criteria, the participant will be thoroughly informed on the designed counseling intervention process, and informed consent will be obtained. If several family members of one COVID-19 victim attend the health center to receive service, only one of them will be enrolled in the study, and the rest will be directed to receive the usual grief counseling services provided at health centers. Assessments will be done at three time points, one before the intervention and the others 1 month and 3 months after the intervention.

### Consent procedure

Participants entering the study will receive oral explanations of the trial intervention and will sign an informed consent form. This is performed by the clinical psychologist of the health center, and they are responsible for responding to any queries. Informed consent will be mainly provided in a general non-technical language, so that it would be comprehensible at any scholastic level. If a participant does not have the necessary inclusion criteria or does not give informed consent to be enrolled in the study, they will be excluded from the study and will receive services as usual. The informed consent method of this study has been approved by the Medical Ethics Committee of the Iran University of Medical Sciences (IUMS) and has been registered with the trial registration number of IRCT20200505047305N1. Participants can exit the trial whenever they wish.

### Randomization

After informed consent, participants are randomized into three- or five-session intervention groups. Allocation of participants to each group will be done with the use of Stratified Balanced Block Randomization. Twelve participants will be selected from each university, and randomization will be done separately for each. Among 20 possibilities for six blocks including forms of three individuals in the five-session group and three individuals in the three-session group, two blocks will be randomly chosen for each university in the Microsoft Office Excel software with the use of the RANDBETWEEN formula and a random sequence will be formed. Subsequently, participants will be divided into the three- and five-session groups equally according to the random sequence. Randomization will be done in the main research headquarters in the Mental Health Research Center of the IUMS, and information will be only given to the health centers at the time of initiation of the intervention.

### Data collection/management process

The primary outcome measure is the grief intensity based on the grief intensity scale (GIS) score of individuals receiving grief counseling sessions after a 3-month follow-up period, and the secondary outcomes are the quality of life, psychological distress, and satisfaction with the services. In this study, one qualified clinical psychologist will be entitled to each medical university attending two of the health centers to collect data at three points of participant entry (baseline assessment) and two follow-up points at 1-month and 3-month follow-up periods. Satisfaction with the services will be assessed at the end of the counseling sessions (either three or five) and 3-month after it. Clinical psychologists who are working as raters will be trained to use the questionnaires, and inter-rater reliability will also be checked after the training sessions. To reduce the risk of research bias, the raters will not be among those clinical psychologists providing the grief counseling sessions and will be blind toward the number of sessions each individual has received.

Demographic variables will be obtained using a questionnaire created by the researcher, and data collection for obtaining the dependent variables of the study will be performed by using the GIS, the General Health Questionnaire (GHQ-28), the Short Form Health Survey (SF-12), and the Client Satisfaction Questionnaire (CSQ-8).

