The study aims at comparing the efficacy of providing three versus five sessions of a grief counseling intervention to family members of those deceased due to COVID-19 in the setting of a multi-center randomized clinical trial. The primary outcome measure is the intensity of grief of individuals after a 3-month follow-up period. Quality of life, psychological distress, and satisfaction with the intervention are the secondary outcomes that will be compared among both groups. In this study, in addition to a general investigation of the efficacy of grief counseling, we aimed to compare the efficacy of three- and five-session grief counseling. If similar efficacy is seen between the two groups due to a lack of resources, three-session counseling can be introduced to the authorities as a population-based intervention for bereaved people in the country. In this case, by spending less time and money, more bereaved people will benefit from this service.

We hypothesize that the effect of the three-session grief counseling intervention on the grief intensity, psychological distress, quality of life, and satisfaction with the intervention among participants will be comparable with the five-session intervention and supposedly have equal efficacy.

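### Satisfaction is timed from the end of the assigned course and early stoppers have no planned rating, so the comparison is of completers and may be biased

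*Protocol article*

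**What the plan says.** Four parts of the article's Methods bear on this.

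- **Timing** (Data collection/management process): "Satisfaction with the services will be assessed at the end of the counseling sessions (either three or five) and 3-month after it". Both ratings are counted from the end of the course.
- **Stopping** (Intervention), after two calls about a missed session: "In case the participant is not willing to cooperate further, they will be excluded from the study". The rule is the same in both groups. Under Inclusion and exclusion criteria, for someone who meets an exclusion criterion during the course: "that individual will be excluded from the study but the necessary and standard therapy will not be withheld".
- **Missed assessments** (Reducing loss to follow-up), after two unsuccessful calls: "the rater will try to fill out the GIS by phone and end the assessment". The CSQ-8 is not part of this fallback.
- **Analysis** (Planned analysis; also the Abstract): intention to treat.

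Satisfaction is a secondary outcome, but the Introduction includes it in the study hypothesis: with three sessions, "satisfaction with the intervention among participants will be comparable with the five-session intervention".

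On the schedules: "In the five-session intervention, sessions will be held once a week" and "In the three-session intervention, sessions will be held every 2 weeks".

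**The concern.** A participant who stops after session 2 never reaches the end of the assigned course. The second rating is counted from the same moment, so it has no defined date for that participant either. The exclusion rule then takes the person out of the study, and the fallback would not ask about satisfaction anyway. No analysis plan can repair this later, because the ratings would not have been collected.

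Satisfaction is more exposed than the other outcomes, since leaving a service is plausibly related to what one thinks of it. If dissatisfied people leave, each arm's mean overstates satisfaction among those randomised. If they leave at different rates in the two arms, the difference between arms is distorted as well. The article plans to use similarity of the arms to recommend the shorter course to the authorities, so a distortion on one of the hypothesised outcomes is worth removing.

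**Working it through.** **What the plan provides for an early stopper**

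| Step | Provision | CSQ-8 obtained? |
|---|---|---|
| Stops attending and declines to continue | Excluded from the study | No |
| Meets an exclusion criterion mid-course | Excluded from the study | No |
| End-of-course rating | Due when the three or five sessions end | Date not reached |
| Second rating | 3 months after that date | No defined date |
| Assessment missed, calls unsuccessful | GIS by telephone, then end | No |

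No route leads to a rating.

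**Inputs from the article.** 60 per arm; 20% drop-out overall (Sample size calculation); two return visits after session 1 in one arm and four in the other. Both courses span 4 weeks: 2 × 2 weeks and 4 × 1 week. There is no drop-out figure by arm and no CSQ-8 standard deviation, so there is no plan figure to reproduce for this outcome. What follows is scenario arithmetic.

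**Scenario A: constant risk q per return visit (assumption).** The proportion lost is 1 − (1 − q)² with three sessions and 1 − (1 − q)⁴ with five. Setting their average to 20% gives q = 0.0726.

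- Three sessions: 1 − 0.9274² = 0.140, about 8 of 60.
- Five sessions: 1 − 0.9274⁴ = 0.260, about 16 of 60.

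**Scenario B: constant risk w per week (assumption).** Both courses last 4 weeks, so loss is 1 − (1 − w)⁴ in both arms. At 20%, w = 0.0543 and 12 of 60 are lost in each arm.

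**Size of the bias.** Assume equal true means, unit SD, and a normally distributed tendency to stop that correlates r with dissatisfaction. If the proportion p most inclined to stop is lost, the mean of those who remain rises by r × φ(z_p)/(1 − p), where z_p is the normal quantile of p.

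- p = 0.140: z = −1.081, φ = 0.2224, ratio 0.2224/0.860 = 0.259.
- p = 0.260: z = −0.643, φ = 0.3245, ratio 0.3245/0.740 = 0.439.
- Difference, five minus three: 0.180 × r.

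| Scenario | r = 0.3 | r = 0.5 |
|---|---|---|
| A: 14% v 26% lost | 0.054 SD | 0.090 SD |
| B: 20% v 20% lost | 0 | 0 |

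In scenario B each arm's own mean is still raised by 0.350 × r (0.280/0.8 = 0.350), that is 0.105 to 0.175 SD, but this cancels in the difference.

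**Cross-check in CSQ-8 points (range 8 to 32).** If stoppers would have scored D points lower, the bias is D × (0.260 − 0.140). For an assumed D of 2 to 6 points this is 0.24 to 0.72 points in scenario A and 0 in scenario B. If loss ran the other way, for example 25% with three sessions and 15% with five, it would be −0.2 to −0.6 points.

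**Scale.** With 60 × 0.8 = 48 raters per arm, the standard error of the difference is about √(2/48) = 0.20 SD. The scenario A bias is about a quarter to under a half of one standard error.

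**The case against.** The strongest objection concerns direction. A reader might infer that more people are lost from the five-session arm, because that course has four return visits against two, and that the comparison is therefore biased towards it. The article does not support this as fact. It gives a single drop-out figure, applies one missed-session rule to both arms, and schedules courses of equal length. Unequal loss follows if the risk attaches to visits and vanishes if it attaches to weeks. Some stopping will also have nothing to do with dissatisfaction, such as exclusion because a criterion is met mid-course. This objection stands: direction and size are unknown.

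Second, the timing sentence does not itself say that only completers are rated. The end of the sessions could mean the end of whatever was attended, and a second rating is planned. That is fair for the sentence alone. Read with the exclusion rule and the GIS-only fallback, however, the plan still has no step that obtains a rating from someone who stopped.

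Third, this may look like nothing more than the general problem of excluding stoppers. The two overlap, but keeping stoppers in follow-up would not by itself fix the gap, because both CSQ-8 dates are defined by the end of the course and the fallback omits the questionnaire.

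Last, the outcome is secondary, the scenario bias is well below one standard error, and a journal article may leave handling of discontinuers to a fuller document. That limits the weight of the point. It does not remove it, because what the article does fix conflicts with its own intention-to-treat statement.

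**Conclusion.** The point holds as a data gap with a possible bias. Followed as written, the plan yields a satisfaction comparison of completers, not of the randomised groups. Whether that biases the difference between arms depends on two things the article does not give: how strongly stopping is related to dissatisfaction, and whether stopping differs by arm. At the stated 20% overall loss, the illustrations run from no between-arm bias (constant weekly risk) to about 0.05 to 0.09 SD in favour of five sessions (constant risk per return visit, correlation 0.3 to 0.5). The opposite sign is possible if more people stop in the three-session arm. The point does not bear on the primary GIS comparison. It is worth correcting because satisfaction is a hypothesised outcome and the correction is cheap.

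**What to change.** Reword the timing sentence so that the first CSQ-8 is requested from every randomised participant 4 weeks after the scheduled date of session 1, and the second 3 months after that date, regardless of sessions attended. Both courses are due to end at 4 weeks, so those on schedule are rated when they would have been anyway. Using the scheduled date, not the attended one, also gives a time point to people who never come to session 1.

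Add the CSQ-8 to the telephone fallback, and state that people who stop counselling are still asked for these ratings if they agree to answer.

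The cost is a small change of wording and an eight-item call to those who stopped; the raters already make follow-up calls. There are two small downsides: some ratings come by telephone, and participants whose sessions slip are rated before their last session. Those who refuse will still be missing, so the number of ratings obtained should be reported by arm.
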